Hypothesis 1 (H1): There will be a reduction in loneliness in participants assigned to the Nextdoor KIND Challenge groups compared to the waitlist control group post the 4-week intervention.Hypothesis 2 (H2): There will be a reduction in social isolation in participants assigned to the Nextdoor KIND Challenge groups compared to the waitlist control group post the 4-week intervention.Hypothesis 3 (H3): There will be an improvement in neighbourhood relationship quality and contact outcomes (a) social cohesion and trust, (b) perception that their neighbourhood is improving, (c) higher importance around getting to know their neighbours, (d) more likely to be classed as having a supportive neighbour network than not, (e) have lower neighbourhood conflict, and (f) increased number of neighbourhood contacts, in participants assigned to the Nextdoor KIND Challenge groups compared to the waitlist control group post the 4-week intervention.Hypothesis 4 (H4): There will be an improvement in mental health secondary outcomes, lower (a) depression and (b) social anxiety, (c) stress, and greater (d) quality of life, and (e) positive affect, in participants assigned to the Nextdoor KIND Challenge groups compared to the waitlist control group post the 4-week intervention.

While it is vital to investigate the impact of KIND Challenge post intervention, it is possible for impact on outcomes to be distal; that is indirect effects caused by changes in proximal outcomes. The KIND Challenge aims to reduce loneliness and social isolation, which may lead to later distal impact on other outcomes. Capturing impact at one-month follow-up after the completion of the KIND Challenge enables modelling the maintenance of intervention effects, i.e., are effects sustained at one-month or are sleeper effects present? In addition to understanding whether effects of the intervention are sustained, it is also important to know whether the intervention itself is sustainable. The KIND Challenge acts are positive, engaging, and feasible to the average individuals, and thus designed to be sustainable.
Hypothesis 5 (H5): The Nextdoor KIND Challenge effects noted in H1–4 above will be maintained at one-month follow-up for the participants randomly allocated to KIND Challenge group.Hypothesis 6 (H6): The KIND Challenge is sustainable, participants assigned to the KIND Challenge will continue engaging in acts of kindness at one-month follow-up.

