#### Neighbourhood perception of change [38]

This question used by a previous study by Bateman and colleagues [38], asks if participants thought their neighbourhood was improving from 1 (improving), 2 (stable) or 3 (declining).

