#### Neighbourhood importance [38]

This question used by a previous study by Bateman and colleagues [38], asks how important participants thought it was to know their neighbours from *1 (very important) to 5 (very important)*.

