#### Neighbourhood number of contacts

This item asks the number of people the participants know in their neighbourhood, 0 (0–5 neighbours) to 4 (15+ neighbours). This question was developed for the study (see Supplementary Table 1 reference b).

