### Secondary outcomes analysis

The above ITT analysis using linear multiple regression modelling in Mplus 8.3, will be repeated for the secondary outcome of social isolation (H2) and the neighbourhood relationship quality outcomes H3 (a) social cohesion and trust (measured using the Social Capital Scale) at post 4-week intervention. For outcomes (b) perception that their neighbourhood is improving (categorised at improving, stable or declining), and (d) supportive, aversive, or ambivalent neighbour network classification, because those are categorical data, we will use a multi-nominal regression. Outcomes (c) higher importance around getting to know their neighbours (high and low importance), (e) neighbourhood conflict (no neighbourhood conflict and instances of neighbourhood conflict), and (f) number of neighbourhood contacts (0–5 and 6+ neighbourhood contacts) are dichotomous categorical data so we will use a binominal regression to explore ITT effects. Similarly, for all mental health secondary outcomes at post 4-week intervention, H4 (a) depression (b) social anxiety, (c) stress, (d) quality of life, and (e) positive affect, measured using the PHQ-8, Mini-SPIN, PSS-4, EUROHIS-QOL-8, and PANAS-PA respectively. The same model building approach will be adopted as in H1.

To model whether effects are maintained for all outcomes (H5) in the participants assigned to the KIND Challenge group, a series of within-group ANCOVAs will be run. Differences in baseline (T1), post-intervention (T2), and one-month follow-up (T3) outcomes will be analysed for both primary and secondary outcomes. A model building approach will be taken controlling co-variates outlined above for H1–4. The sustainability of the intervention (H6) will be explored to determine if the participants assigned to the KIND Challenge group continue with acts of kindness. Both the frequency and duration of KIND acts completed in the one-month follow-up, and the level of engagement for each type of activity completed (i) emotional support, (ii) tangible support, (iii) informational support, (iv) belonging support, and (v) companionship support will be analysed. A series of within-group ANCOVAs will be run using the frequency and duration of KIND acts completed post 4-week intervention and one-month follow-up, to determine if engagement is sustained.

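### H3(c) importance and H3(f) number of contacts are collected as ordered multi-level items but analysed as dichotomies, so the contacts analysis cannot register an increase in anyone already at six or more

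*Protocol article*

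**What the plan says.** Hypothesis 3 lists six neighbourhood outcomes. Three bear on this point.

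- **Contacts, H3(f).** The prediction is an "increased number of neighbourhood contacts". Under Neighbourhood number of contacts: "This item asks the number of people the participants know in their neighbourhood, 0 (0–5 neighbours) to 4 (15+ neighbours"). Under Secondary outcomes analysis: "number of neighbourhood contacts (0–5 and 6+ neighbourhood contacts) are dichotomous categorical data so we will use a binominal regression to explore ITT effects".
- **Importance, H3(c).** The item "asks how important participants thought it was to know their neighbours from" 1 to 5. The same analysis sentence reduces it to high and low importance and classes it as dichotomous.
- **Perception of change, H3(b).** Responses are "1 (improving), 2 (stable) or 3 (declining"). With the neighbour-network classification, H3(d), it is analysed as follows: "because those are categorical data, we will use a multi-nominal regression".

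The only reason given for the binary models is that the data are dichotomous. No full-scale analysis of contacts or importance is described. Under Statistical methods, every analysis is run separately by country.

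**The concern.** The choice of model rests on a description of the data that the measures sections contradict. Contacts and importance become dichotomous only because the analysis makes them so.

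For contacts, the cut also parts company with the hypothesis. H3(f) is about knowing more neighbours, while the analysed variable records only whether someone is above the lowest band. If the intervention moves people from a middle band to the top one, the planned contrast is zero. A null result could then be read as no effect on contacts, when the test could not see change above the first boundary.

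The second stake is power. Two groups never carry more information about a common shift than the full ordered scale, and may carry much less.

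**Working it through.** **1. The article's own figure.** The only power statement is the minimum detectable effect of 0.14 for loneliness. Inputs from Sample size: 1500 per country, 20 covariates, pre-post correlation 0.35, power 0.80, alpha 0.05 (two-sided assumed). With df = 1478 and R² = 0.35² = 0.1225:

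MDES = (1.962 + 0.842) × √[(1 − 0.1225)/(0.25 × 1500)] = 2.803 × 0.0484 = 0.136, which rounds to 0.14.

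It reproduces and is not in dispute. No power is stated for any H3 outcome.

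**2. What the cut can and cannot see (no assumption needed).** For someone at 6+ at baseline, the analysed value is already the higher one. Any rise leaves it unchanged; only a fall to 0–5 alters it. To illustrate, take assumed four-band shares of 0.40, 0.25, 0.15, 0.20 in one arm and 0.40, 0.19, 0.16, 0.25 in the other. The binary difference is exactly zero. A rank test on the full scale has 31% power with 750 per arm (1000 simulations). That is not high, but the binary analysis has no effect to find.

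**3. Power cost under a common shift.** *Assumptions, because the article gives no category distribution:* common odds ratio 1.3, 750 per arm (1500 per country, 1:1), no attrition, two-sided 5%, no baseline adjustment in either analysis. Four bands are used except where stated. The codes 0 to 4 imply five levels, but bands as wide as the first, running up to 15+, suggest four.

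Ordinal power (Whitehead's proportional-odds formula) = Φ{ln(1.3) × √[750 × (1 − Σp̄³)/6] − 1.96}, where p̄ is the mean share per band over the two arms. Binary power is the usual two-proportion formula.

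*15% of controls in 0–5* (shares 0.15, 0.25, 0.25, 0.35):
- Ordinal: Σp̄³ = 0.0862; 0.2624 × √(750 × 0.9138/6) = 2.804; Φ(0.844) = 80%.
- Binary: 6+ rises from 0.850 to 0.8805, since odds 5.667 × 1.3 = 7.367. Then Φ[(0.0305 − 1.96 × 0.0176)/0.0176] = 41%.

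*80% of controls in 0–5* (0.80, 0.10, 0.05, 0.05):
- Ordinal: Σp̄³ = 0.4714; 0.2624 × √(750 × 0.5286/6) = 2.133; Φ(0.173) = 57%.
- Binary: 0.200 to 0.2453; Φ[(0.0453 − 1.96 × 0.0215)/0.0215] = 56%.

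| Control share in 0–5 | Binary power | Ordinal power | Efficiency (ordinal n / binary n) |
|---|---|---|---|
| 15% | 41% | 80% | 0.38 |
| 25% (four even bands) | 57% | 81% | 0.56 |
| 30% | 62% | 81% | 0.64 |
| 40% | 69% | 80% | 0.76 |
| 50% | 72% | 79% | 0.85 |
| 60% | 71% | 75% | 0.91 |
| 80% | 56% | 57% | 0.98 |
| 20% (five even bands) | 50% | 82% | 0.46 |

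**4. Importance, same assumptions.** The position of the high/low cut is not given, so it is varied.
- Assumed shares 0.05, 0.10, 0.25, 0.35, 0.25: 41% binary with 15% below the cut, 69% with 40% below, against 80% ordinal.
- Five even levels, cut after the second or third: 69% or 71%, against 82% ordinal.

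**The case against.** The strongest reply is that the size of the loss is unknown. If most participants know five or fewer neighbours, the planned cut costs almost nothing. The calculation also assumes a common odds ratio, which favours the ordinal model. If the effect fell mainly on people with few contacts, the lowest cut would capture most of it and the ordinal advantage could shrink or reverse. A binary contrast needs no proportional-odds assumption and is easy to explain. Neighbour ties are also measured by the six-item neighbour subscale of the Lubben scale, which is analysed linearly for H2. All of this stands. It limits the claim to a range and supports keeping the splits in a supporting role. It does not make the items dichotomous, and the article does not offer this rationale for the cut.

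A reader might infer four stronger points that the article does not support.

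- *The cut hides every change among those at 6+.* It hides rises and moves within 6+; a fall to 0–5 still shows. Changes within 0–5 are lost at data collection, and no model recovers them.
- *Multinomial regression is wrong for perception of change.* It is valid for three categories and can address whether the neighbourhood is seen as improving. A two-degree-of-freedom overall test would be less powerful than an ordinal one, but Outcomes analysis judges effects by the trial-group coefficients, so such a comparison is not the power of the stated test.
- *The importance item cannot be analysed because it is printed as* "1 (very important) to 5 (very important"). This is evidently a wording slip at one end. The unstated cut-point is detail that an analysis plan may supply.
- *The other H3 outcomes share the fault.* The network classification, H3(d), is nominal, and conflict, H3(e), is any versus none across yes/no items.

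**Conclusion.** The point holds for H3(c) and H3(f). Both are described as dichotomous although they are collected as ordered multi-level items. For H3(f), the cut also prevents the analysis from registering the predicted increase in anyone already above the lowest band; that follows from the text alone.

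The power cost is a range, not a figure. At an assumed odds ratio of 1.3 with 750 per arm, it runs from about one percentage point (80% of controls in 0–5) to about 39 points (15% in 0–5). The binary cut was less efficient in every distribution tried, with efficiency from 0.38 to 0.98, but all of them assume a common odds ratio. For H3(b), an ordinal model is an optional gain in efficiency, not a correction. The change is worth making, but it affects only the power and interpretation of single-item secondary outcomes; the primary result does not depend on it.

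**What to change.** Make the main analysis of H3(c) and H3(f) a proportional-odds regression on all recorded levels, with arm, the baseline level of the same item, gender and age group as terms. Keep the 0–5 versus 6+ and high versus low splits as a prespecified supporting analysis, since they do not need the proportional-odds assumption. If proportionality does not hold exactly, read the ordinal odds ratio as an average effect across the cut-points. Do not switch models after a test of the assumption: that would add data-dependent choices across three countries and four covariate models. In the same edit, remove the description of these two items as dichotomous, state the number of contact bands and correct the importance anchor. An ordinal model for H3(b) may be added if wanted.

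The cost is analysis wording only, with no new data. The downside is reliance on the proportional-odds assumption, which the retained binary analysis offsets.

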#### Social relationship index - Neighbourhood modified [39, 40]

The 3-item scale was modified from the Social Relationship Index (SRI) which measures both positivity and negativity in relationship ties which can indicate if one has supportive, ambivalent, or aversive ties [39, 40]. We ask participants how helpful, upsetting, and mixed/conflicted their feelings are towards their neighbours when needing advice, understanding, or a favour – rated on a Likert scale from 1 (not at all) to 6 (extremely). Based on these scores and using a threshold model classification, participants are then categorised to either having a supportive, aversive, or ambivalent neighbour relationship.

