### Adherence and engagement variability

Variability in adherence and engagement will be measured in the participants allocated to the KIND Challenge group. First, adherence can be measured by the frequency and duration of KIND acts completed during the 4-week intervention. Second, an index of level of engagement for each type of activity completed (i) emotional support, (ii) tangible support, (iii) informational support, and (iv) belonging support, (v) companionship support can be created by combining the frequency and duration to produce an indicator of dosage for each type of KIND act. Third, the impact of overall engagement with the KIND Challenge can be modelled via meaningfulness, degree of positive feelings and sense of connectedness to others.

Linear multiple regression modelling in Mplus 8.3, will be employed to model the adherence and engagement as predictors of post 4-week intervention outcomes (H7), across the primary outcome of loneliness, and secondary outcome of social isolation, a neighbourhood relationship quality and contact, neighbourhood connectedness, and mental health. As with the H1–4 the model building approach will be used.

Reasons for non-compliance will also be captured and explored to assess barriers and challenges to competing the KIND activity, as measured by frequencies of lack of time, forgot, illness, work stress, family pressures or other.

CACE estimation will be employed using Mplus 8.3 to examine whether the effects noted in ITT analyses (H1–4) change once intervention compliance is taken into account. Participant demographics and baseline outcome variables will be used as predictors of the latent class compliance variable. Compliance will be assessed via dosage (i.e., number of kind acts completed; compliers vs. non-compliers). The CACE analysis will follow the same regression model building approaches detailed in H1–4.

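### H5 (ANCOVA) and H7 (linear regression) are applied to outcomes the protocol itself treats as categorical; for the supportive/aversive/ambivalent class the result depends on arbitrary codes

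*Protocol article*

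**What the plan says.** Four places in the protocol article bear on this.

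- **H3 models (Secondary outcomes analysis).** The between-arm analysis sorts outcomes by data type. For (b) perception of neighbourhood change and (d) the neighbour-tie class, "because those are categorical data, we will use a multi-nominal regression". Outcomes (c) importance, (e) conflict and (f) number of contacts are called dichotomous and get binomial regression. Only (a), social cohesion and trust, gets linear regression.
- **H5 model (next paragraph of the same section).** The text reads "To model whether effects are maintained for all outcomes (H5) in the participants assigned to the KIND Challenge group, a series of within-group ANCOVAs", and the sentence after it adds that the baseline, post-intervention and follow-up "outcomes will be analysed for both primary and secondary outcomes". As worded under Objectives, H5 is that "The Nextdoor KIND Challenge effects noted in H1–4 above will be maintained at one-month follow-up", so all six H3 outcomes fall within it.
- **H7 model (Adherence and engagement variability).** "Linear multiple regression modelling in Mplus 8.3, will be employed to model the adherence and engagement as predictors of post 4-week intervention outcomes (H7"). The outcomes listed include "secondary outcome of social isolation, a neighbourhood relationship quality and contact, neighbourhood connectedness, and mental health". A closing sentence says that the model-building approach of H1–4 will be used.
- **Nature of H3(d) (Social relationship index – Neighbourhood modified).** From three item ratings, "participants are then categorised to either having a supportive, aversive, or ambivalent neighbour relationship". No numeric order is given to the three classes.

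**The concern.** ANCOVA and linear regression need a numeric outcome. The protocol recognises this for H3, and again under Statistical methods, where baseline balance uses MANOVA for interval data and chi-square for nominal data. For H5 and H7 it names a single linear model for outcomes it has just said need another kind. A statistical analysis plan could not supply this as missing detail, because the article states a model and the stated model conflicts with its own rule.

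For H3(d), following the text literally means inventing code numbers for three unordered classes. The reported change (H5) or slope (H7) would then reflect the analyst's choice of codes as well as the data. H5 is the protocol's stated test that H1–4 effects last to one month, and for this outcome it could not give a meaningful answer.

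**Working it through.** The documents give no figure to reproduce here. The check compares the models named, counts the outcomes affected, and tests how far the answer depends on coding.

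**1. Models named, by outcome**

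| H3 outcome | Type | H3 model | H5 model | H7 model |
|---|---|---|---|---|
| (a) cohesion and trust | scale score | linear | ANCOVA | linear |
| (b) perception of change | three ordered levels | multinomial | ANCOVA | linear |
| (c) importance | two-level | binomial | ANCOVA | linear |
| (d) tie class | three unordered classes | multinomial | ANCOVA | linear |
| (e) conflict | two-level | binomial | ANCOVA | linear |
| (f) contacts | two-level | binomial | ANCOVA | linear |

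Five of the six rows conflict. The levels of (b) are ordered because its item is coded 1 improving, 2 stable, 3 declining (Neighbourhood perception of change).

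**2. H5 for (d): does the mean depend on the codes?** With class shares p and codes c, mean = Σ c·p and change = Σ c·(p at follow-up − p at baseline). The documents give no shares, so those below are assumptions.

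Shares supportive/aversive/ambivalent of 60/10/30% moving to 66/10/24%:

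- Supportive = 1, aversive = 2, ambivalent = 3: 0.60 + 0.20 + 0.90 = 1.70, then 0.66 + 0.20 + 0.72 = 1.58. Change −0.12, towards supportive.
- Ambivalent = 1, supportive = 2, aversive = 3: 0.30 + 1.20 + 0.30 = 1.80, then 0.24 + 1.32 + 0.30 = 1.86. Change +0.06, which reads as a move towards aversive although the aversive share stays at 10%.

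A second set, 50/20/30% moving to 50/10/40%, with 750 participants in the Challenge arm (half of the planned 1500 per country). F is approximated as change² ÷ [(variance at baseline + variance at follow-up)/750], treating the two time points as independent:

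| Class given the middle code | Change (sign depends on direction of coding) | Approximate F |
|---|---|---|
| aversive | ±0.10 | 4.55 |
| ambivalent | ±0.10 | 7.14 |
| supportive | ±0.20 | 33.33 |

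Allowing for within-person correlation would change the F values but not the mean changes.

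**3. H7 for (d): does the slope depend on the codes?** One simulated data set, n = 750, had a standard normal engagement score x. The assumed log-odds against supportive were −0.9 − 0.4x for aversive and −0.5 + 0.4x for ambivalent. The linear slope was ±0.072 (p = 0.015), ±0.121 (p = 0.0002) or ±0.192 (p = 2.6 × 10⁻¹³), depending only on the coding. Multinomial regression gave one likelihood-ratio result (p = 2.2 × 10⁻¹²), which does not depend on the code numbers.

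**4. Two-level outcomes.** In a simulated binary outcome, codes 0/1 and 1/2 both gave a slope of 0.075 with p = 4.9 × 10⁻⁵. Reversing the labels changed only the sign. The arbitrary-code problem does not arise.

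**5. Count.** The arbitrary-code defect covers 1 outcome × 2 hypotheses × 3 separately analysed countries = 6 sets of analyses.

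**The case against.** Several points on the other side have force.

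- **A reader might infer that all five categorical outcomes give meaningless results, in 5 × 2 × 3 = 30 sets of analyses.** The documents do not support that. Outcome (b) is ordered, so its direction can be read and only equal spacing is assumed. Outcomes (c), (e) and (f) are two-level, and a linear model for them estimates a difference in proportions. For these four the defect is inconsistency with the H3 models and a different scale.
- **A reader might add that the binary outcomes would have invalid standard errors.** Statistical methods provides for estimators robust to non-normality, such as MLR, and robust errors are the usual remedy for unequal variances in a linear probability model. They cannot turn a nominal class into a scale.
- **A reader might conclude that H1–4 effects could not be followed to one month at all.** H5 compares three time points within one arm on one scale, so the change from post-intervention to follow-up can be read inside H5. It remains a within-arm contrast whichever link function is used.
- **H3(d) may be meant as two-level.** Objectives words it as being more likely to have a supportive network than not, which needs no arbitrary coding. But Secondary outcomes analysis keeps three classes, and nothing says that H5 or H7 collapses them.
- **H7 may be shorthand.** Its closing sentence resembles the one for the complier (CACE) analysis, which follows the regression approaches of H1–4. Under Outcomes analysis, however, model building means the covariate steps, Models 1 to 4, and the only H7 model named is linear. The literal reading supports the point, but the sentence is ambiguous. It does nothing for H5, where ANCOVA for every outcome is explicit.

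**Conclusion.** The point stands in this form. The protocol's data-type rule for H3 is contradicted by its H5 text and, on the most literal reading, by its H7 text. The contradiction matters most for H3(d), where both the sign and the size of the result depend on arbitrary codes, in 6 sets of analyses. For (b), (c), (e) and (f) it is an inconsistency that leaves interpretable results.

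The class shares and slopes used above are illustrative assumptions. The dependence on coding does not rest on them, because it follows from putting an unordered class into a linear model. The H5 limb is firm and the H7 limb somewhat less so.

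This should be corrected but is not critical. The primary loneliness analysis and the intention-to-treat analyses of H2–4 are untouched. H5 is a within-arm maintenance question, and the protocol describes H7 as exploring moderation.

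**What to change.** - **Secondary outcomes analysis, H5:** limit the within-group ANCOVAs to the continuous outcomes. Analyse H3(b) to (f) with repeated-measures categorical models: GEE or mixed logistic for (c), (e) and (f); ordinal or multinomial for (b); and for (d) either multinomial or a binary supportive-versus-not outcome, as H3(d) is worded under Objectives.
- **Adherence and engagement variability, H7:** state that (b) to (f) use the same model families as in H3, and that the covariate steps of H1–4 are added to those models.

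The cost is a short change of wording in two sections and slightly more modelling work. No new data are needed.

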#### Acceptability

We measure acceptability around these factors, including how connected (1 not at all connected to 10 very connected), how meaningful was the KIND Challenge activity (1 not very meaningful to 10 very meaningful), how safe they felt when completing the KIND Challenge (1 not very safe to 10 very safe), how positive they felt (1 not very positive to 10 very positive), how comfortable they felt doing the KIND Challenge activity (1 not at all comfortable to 10 very comfortable). It is anticipated that the Nextdoor KIND Challenge will yield ratings of more than 5 indicating higher levels of acceptability across these outcomes. These questions were specifically developed for the study (see Supplementary Table 1 section c).

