#### Safety

We assess for unintended harms (e.g., conflict) during this period. In this case, we measure the occurrence of neighbor conflict because of the KIND Challenge. It is anticipated that the KIND Challenge activity is safe for participants with no unintended conflicts reported. This question was developed for the study (see Supplementary Table 1 section d).

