#### Follow up KIND challenge activity

At 1 month follow-up**,** participants will be asked if they have been in contact with their neighbours in the past month (Yes/No). Participants are asked if they have *continued* with the Kindness activity, if so, which activity or activities they chose to continue. Participants will be asked how frequently they completed the activity (1 = once to 4 = more than 5 times), the duration (1 = less than 10 min to 5 = more than 2 h), and how connected they felt to others after completing the activity (1 = not at all to 10 = very). If they had not continued a Challenge activity, participants will be asked to report the main reasons for not continuing with the KIND Challenge activity in a textbox provided. These questions were specifically developed for the study (see Supplementary Table 1 – section f).

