For feasibility, acceptability, and safety, we will present the descriptive statistics on these indicators (feasibility = < 40% drop out; acceptability more than 5 or higher on meaningful, safe, positive, and comfort ratings; and no reported conflicts because of doing the KIND challenge).

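### The sustainability analysis (H6) uses scales that only people still doing acts of kindness can answer, and the acceptability threshold is stated in two different ways

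*Protocol article*

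**What the plan says.** **H6.** In the Protocol article, Objectives, Hypothesis 6 states that "participants assigned to the KIND Challenge will continue engaging in acts of kindness at one-month follow-up". The section Secondary outcomes analysis repeats the aim, "to determine if the participants assigned to the KIND Challenge group continue with acts of kindness", and then names the method: "A series of within-group ANCOVAs will be run using the frequency and duration of KIND acts completed post 4-week intervention and one-month follow-up".

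The follow-up variables are defined under Follow up KIND challenge activity. Participants are asked whether they have continued "with the Kindness activity, if so, which activity or activities they chose to continue". Frequency is then rated from 1 (once) to 4 (more than 5 times) and duration from 1 (less than 10 min) to 5 (more than 2 h). The other branch reads: "If they had not continued a Challenge activity, participants will be asked to report the main reasons for not continuing". The section Post-KIND challenge activity uses the same two scales after the intervention and sends participants who did no activity to a multiple-choice question on reasons.

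**Acceptability.** The section Acceptability lists five ratings on 1 to 10 scales (connected, meaningful, safe, positive, comfortable) and says: "It is anticipated that the Nextdoor KIND Challenge will yield ratings of more than 5 indicating higher levels of acceptability across these outcomes". The closing paragraph of Secondary outcomes analysis gives the criteria again: "acceptability more than 5 or higher on meaningful, safe, positive, and comfort ratings; and no reported conflicts because of doing the KIND challenge".

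**The concern.** H6 concerns everyone assigned to the Challenge, and its central question is whether they carry on at all. The outcomes named for it exist only for people who did at least one act in the period. Someone who stopped has no frequency or duration at follow-up, and the stated scales have no value for none. The yes/no continuation item, which answers the question directly, is not part of the named analysis. A comparison conditioned on continuing says how active the continuers were, not whether the arm continued. The conclusion on whether the intervention is sustainable depends on this.

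For acceptability, the Objectives section refers the reader to criteria set in advance. Two versions of such a criterion leave the authors free to choose between them after seeing the ratings.

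**Working it through.** The plan gives no figure for continuation or for ratings, so there is no plan figure to reproduce. The rates below are assumptions.

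**H6: who has a value**

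| Participant | Post-intervention | One-month follow-up |
|---|---|---|
| Did acts, continued | frequency 1–4, duration 1–5 | frequency 1–4, duration 1–5 |
| Did acts, stopped | frequency 1–4, duration 1–5 | reasons only |
| Did no act | reasons only | no zero value stated |

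Only the first row supplies a pair of values.

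**H6: size.** Let c be the share of responders who continue and g the relative change in frequency among them. Assume continuers and stoppers had the same mean frequency after the intervention.

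- Change among continuers = g
- Change over all responders, stoppers at 0 = c(1 + g) − 1

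| c | g | Continuers only | All responders |
|---|---|---|---|
| 0.8 | 0 | 0% | −20% |
| 0.5 | 0 | 0% | −50% |
| 0.4 | 0 | 0% | −60% |
| 0.2 | 0 | 0% | −80% |
| 0.5 | −10% | −10% | 0.5 × 0.9 − 1 = −55% |

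On the coded scale, take an assumed post-intervention distribution of 40/30/20/10% over categories 1 to 4. The mean is 0.4 + 0.6 + 0.6 + 0.4 = 2.0. With 40% continuing unchanged, the all-responder mean is 0.4 × 2.0 = 0.8, a change of −1.2. A simulated sample of 450 with this distribution gave −1.17 when stopping was unrelated to earlier frequency, and −1.03 when those who had done more were likelier to continue. The continuers-only change is 0 in both, because unchanged frequency was assumed.

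**H6: would the missing-data plan cure this?** The Missing data section offers complete-case analysis below 5% missing and full information maximum likelihood under missing at random above it. The first drops stoppers. The second, on a scale starting at once, would model them as though they had acted. Their true value is known to be none, so it is not missing.

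**H6: survey non-response is a different matter.** With 1500 per country and 1:1 allocation, about 750 are in the KIND arm. At the 40% drop-out limit, 750 × 0.6 = 450 respond. If half of these continue (assumed), that is 225:

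- Among responders: 225/450 = 50%, 95% interval about ±1.96 × √(0.25/450) = ±4.6 points
- Of all allocated, if no non-responder continued: 225/750 = 30%
- Of all allocated, if every non-responder continued: (225 + 300)/750 = 70%

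Non-responders should therefore be neither scored as zero nor left out of sight.

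**Acceptability, side by side**

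| | Acceptability section | Secondary outcomes analysis |
|---|---|---|
| Cut-off | above 5 | above 5, or 5 and above |
| Items | five, including connected | four, connected absent |

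The scale midpoint is (1 + 10)/2 = 5.5, so admitting 5 passes a below-midpoint rating. Applied per person, the two cut-offs differ by the share answering exactly 5. On a uniform distribution that is 50% against 60%. In an assumed distribution with 18% at 5, it is 65% against 83%. Applied to a mean rating, they differ only if the mean is exactly 5.

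**The case against.** The strongest reply on H6 is that the restriction to continuers is inferred. The plan states the right aim, collects the yes/no continuation item, and nowhere forbids a zero for non-continuers. The section Adherence and engagement variability builds a dosage index for each activity type and classes people as compliers by number of acts, which implies that not acting must be scored somehow. Coding of skipped items is often left to an analysis plan. It stands that a zero code is not excluded, and that the 0% against −50% contrast needs both stoppers to be dropped and continuers to hold steady. But this is more than an omitted coding detail: the article names the variables and the model, and as named they do not use the item that answers the hypothesis.

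On acceptability, the indicators are descriptive, with no test attached, and on mean ratings the cut-offs almost never differ. That stands too and makes the matter small. The mismatch in item lists remains under either use.

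A reader might also infer that safety is a pass/fail rule which a single conflict report would fail. On assumed true rates, the chance of at least one report, 1 − (1 − p)^n with n = 450 to 750, is 36–53% at p = 0.1% and 90–98% at p = 0.5%. The documents do not support that reading. The Safety section words it as an expectation ("It is anticipated that the KIND Challenge activity is safe for participants with no unintended conflicts reported"), the results are to be presented descriptively, and no conflict rate is given. Nor is the waitlist comparison neglected: neighbourhood conflict is outcome H3(e), is measured in both arms, and has a planned regression for KIND against waitlist after four weeks.

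**Conclusion.** The point holds for H6 and, as a smaller matter, for acceptability.

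For H6, the planned within-group comparison is conditioned on continuing and can report sustained engagement when many assigned participants have stopped. The gap equals the share who stop if continuers' frequency is unchanged: 20 percentage points if 80% continue, 50 if half do. These continuation rates are assumed. It would be too strong to say that H6 will give a wrong answer, since a zero code may yet be applied and continuers' own activity may fall.

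For acceptability, the two statements contradict each other on cut-off and items, and the second contradicts itself. The result is not uniquely defined, though the cut-off matters in practice only if applied to individuals.

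Neither issue touches the primary outcome or a between-arm estimate. They affect the conclusions on sustainability and acceptability, and the plan should be corrected before those are reported.

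**What to change.** **H6.** Make the main result the proportion of KIND-allocated participants who report continuing at one-month follow-up, with a confidence interval. Show survey non-response separately and do not assume it to be zero. In the comparison of frequency and duration between post-intervention and follow-up, enter responders who report no act as 0, at either time point. Use a model suited to zeros and ordered categories, since the codes are categories and not counts.

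**Acceptability.** Reconcile the two statements to one cut-off and one item list, and say whether the cut-off applies to mean ratings or to each individual's rating.

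**Cost.** No new data are needed: the continuation item and all five ratings are already collected. The work is recoding and wording, and the sustainability figure may look less favourable.
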